### Planned Statistical Analysis

Comparisons will be performed between the groups at baseline and after the 36-week treatment phase. The normality of distribution of all continuous variables will be determined using a normality plot and the Kolmogorov-Smirnov test. Normally distributed variables will be analysed using unpaired t-tests, χ^2 ^or repeated measures analysis of variance with corrections made for multiple comparisons. Variables not normally distributed will be log transformed prior to analysis to achieve normal distribution or, if this is not achieved, analysed by Mann-Whitney U or Kruskal-Wallis tests. Multiple linear regression models will be derived for left ventricular mass and measures of vascular and cardiac stiffness using stepwise regression analysis. Analysis will be by intention-to-treat. A p-value of <0.05 will be considered statistically significant.

Sample size calculations were based on the primary endpoint of change in left ventricular mass after 40 weeks of treatment. A previous study by our group evaluating the cardiovascular effects of spironolactone in patients with early CKD revealed a 14 g drop in left ventricular mass from baseline following 40 weeks of therapy [38]. Using data from this previous study, 55 subjects in each arm will provide at least 80% power of detecting an 8 g difference between the change in left ventricular mass from baseline to 40 weeks using a two-tailed t-test at the 5% significance level given a standard deviation of 15 g in the change in left ventricular mass from baseline. Recruiting 60 subjects to each group will allow a 10% withdrawal or dropout rate.

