### Endpoints

The primary end-point of the study will be a reduction in left ventricular mass after 40 weeks of treatment. Left ventricular mass is a powerful predictor of cardiovascular and all-cause mortality in the general population[39] and in CKD [40]. A therapeutic reduction in left ventricular mass has been shown to effectively reduce cardiovascular morbidity and mortality [41,42]. Secondary end points are: i) change in aortic compliance measured by CMR; ii) change in arterial stiffness as assessed using pulse wave velocity and pulse wave analysis; iii) change in arterial elastance measured by echocardiography; iv) change in left ventricular systolic and diastolic elastance measured by echocardiography; v) change in left ventricular function as assessed by tissue Doppler imaging, strain and strain rate analysis and measurement of torsion; and vi) change in bone density on DEXA scanning and/or magnetic resonance imaging.

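### The analysis paragraph assigns no test to the primary endpoint and names no baseline adjustment; the implied t-test on change is valid, but ANCOVA on baseline left ventricular mass gains precision at no cost

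*Protocol article*

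**What the plan says.** The Planned Statistical Analysis section of the protocol article opens: "Comparisons will be performed between the groups at baseline and after the 36-week treatment phase". It then lists its tools: "Normally distributed variables will be analysed using unpaired t-tests, χ^2 ^or repeated measures analysis of variance with corrections made for multiple comparisons". Non-normal variables are to be log transformed or, failing that, analysed by rank tests. The only regression mentioned is stepwise: "Multiple linear regression models will be derived for left ventricular mass and measures of vascular and cardiac stiffness using stepwise regression analysis".

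The Endpoints section words the primary endpoint as follows: "The primary end-point of the study will be a reduction in left ventricular mass after 40 weeks of treatment". All six secondary endpoints there are written as changes. The sample-size paragraph also speaks of change ("Sample size calculations were based on the primary endpoint of change in left ventricular mass after 40 weeks of treatment"). It powers the trial for "detecting an 8 g difference between the change in left ventricular mass from baseline to 40 weeks" with a two-tailed t-test at 5%, "given a standard deviation of 15 g in the change in left ventricular mass from baseline".

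Nowhere does the article say which listed test, or which term of the repeated-measures ANOVA, decides the primary endpoint. No baseline covariate is named.

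**The concern.** The endpoint and sample size concern a between-arm difference in change, whereas the sentence on comparisons speaks of groups at time points. Three things follow.

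- **The deciding test is open.** The wording admits a t-test on change, a t-test on raw week-40 values, and more than one ANOVA term. These do not have the same power.
- **Baseline is collected but not committed to the model.** Left ventricular mass is measured on every subject before the run-in, hence before randomisation. A t-test on change subtracts baseline with a fixed coefficient of 1. ANCOVA estimates that coefficient, so it removes more residual variance and adjusts for chance baseline imbalance. A change score leaves such imbalance to regression to the mean.
- **A between-group test at baseline is uninformative about efficacy.** In a randomised trial it says nothing about the treatment effect.

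At stake is some precision on the primary endpoint, and a clear statement in advance of which test is primary.

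**Working it through.** **Inputs from the Planned Statistical Analysis section:** difference d = 8 g; SD of change 15 g; two-sided 5%; 55 per arm for at least 80% power; 60 per arm recruited with 10% loss, leaving 60 × 0.9 = 54 analysed per arm.

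**Assumed, not in the documents:** correlation ρ between baseline and week-40 mass, taken over 0.5 to 0.95, with equal SDs at the two times.

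**1. The plan's own figure.** Normal approximation: n = 2 × (1.960 + 0.842)² × 15² / 8² = 55.2, so 56 per arm; the exact t calculation gives 57. Power at 55 per arm is 79.9% (normal) or 79.2% (noncentral t). The stated 55 and 80% are reproduced to within rounding. They follow from the SD of change, so the plan was powered for a test on change.

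**2. SDs implied by the stated SD of change.**
- Single-occasion SD: σ = 15 / √(2(1 − ρ)).
- ANCOVA residual SD: σ√(1 − ρ²) = 15 × √((1 + ρ)/2), which is below 15 for any ρ below 1.

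For example, at ρ = 0.8, σ = 15 / √0.4 = 23.7 g and the ANCOVA SD is 15 × √0.9 = 14.2 g.

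**3. Power at 54 per arm.** Noncentrality = 8 / (SD × √(2/54)), with 106 degrees of freedom for the t-tests and 105 for ANCOVA. For the change score this is 8 / (15 × 0.19245) = 2.77, giving 78.4%.

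| ρ | ANCOVA SD (g) | ANCOVA power | Change-score power | Gain (points) | σ (g) | Raw week-40 power |
|---|---|---|---|---|---|---|
| 0.5 | 13.0 | 88.7% | 78.4% | 10.3 | 15.0 | 78.4% |
| 0.7 | 13.8 | 84.6% | 78.4% | 6.2 | 19.4 | 56.6% |
| 0.8 | 14.2 | 82.5% | 78.4% | 4.1 | 23.7 | 41.2% |
| 0.9 | 14.6 | 80.4% | 78.4% | 2.0 | 33.5 | 23.3% |
| 0.95 | 14.8 | 79.4% | 78.4% | 1.0 | 47.4 | 14.0% |

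Raw week-40 values match the change score at ρ = 0.5, where σ = 15, and do worse at any higher ρ.

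**4. Repeated-measures ANOVA with two occasions.** The group-by-time interaction is the t-test on change: in a simulated data set, t² and the interaction F were both 8.70. The group main effect averages in the pre-randomisation value, so the 8 g difference becomes 4 g, with SD σ√((1 + ρ)/2). At 54 per arm its power is about 21%, 15% and 10% at ρ = 0.7, 0.8 and 0.9.

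**5. Measures also taken at the end of run-in.** The Randomisation and Treatment Phase section repeats pulse wave velocity and pulse wave analysis before randomisation. For these, two of the three occasions are pre-randomisation, and both values can serve as covariates.

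**The case against.** The strongest defence is that the powered comparison is already stated. The sample-size paragraph names the change, its SD and a two-tailed t-test, and the secondary endpoints are all changes. Read together, the unpaired t-test most naturally means a t-test on change, and the sentence on comparisons may only describe a baseline table followed by an outcome comparison. The usual treatment test in a two-occasion repeated-measures ANOVA is the interaction, which is the same test. In a randomised trial the change-score test is unbiased over randomisation, so preferring ANCOVA is a choice between valid methods. The article is also condensed, and the analysis plan, which may fix covariates, is not shown.

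Most of this stands. A reader might infer that the trial will test raw week-40 values, or the ANOVA group main effect, and so has far less power than planned. The documents do not support that: the wording allows those readings but does not commit to them, and the sample-size text argues against them. Nor can it be said that baseline is excluded as a covariate, because the regression terms are not listed.

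The objection does not remove two facts. The published paragraph lists several tests without tying one to the powered quantity, and stepwise selection does not guarantee that treatment and baseline both stay in the model.

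**Conclusion.** The point holds as a free improvement, not a must-fix. The implied primary analysis, a t-test on change, is valid and consistent with the sample size. ANCOVA would raise power from 78% to between 79% and 89% with 54 per arm, a gain of about 1 to 10 points that shrinks as the correlation rises. These figures assume a true difference of 8 g, an SD of change of 15 g, equal SDs at the two times, and correlations from 0.5 to 0.95 that the article does not give. At correlations of 0.9 or more the gain is 2 points or less, and adjustment for chance baseline imbalance is then the main benefit. The low power of a raw week-40 comparison or a group main effect is a reason to rule those tests out explicitly; it is not evidence that they are planned.

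**What to change.** In Planned Statistical Analysis:

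- State the primary analysis as ANCOVA of week-40 CMR left ventricular mass (g) on randomised arm, with pre-run-in baseline CMR mass as covariate. Report the adjusted difference with its 95% CI. The article also measures mass by echocardiography, so CMR should be named.
- Use the same model for each continuous secondary endpoint. Where a measure is repeated at the end of run-in (pulse wave velocity, pulse wave analysis), add that value as a second covariate.
- State that neither between-group tests at baseline nor a repeated-measures group main effect will serve as efficacy tests, and that the stepwise models are exploratory.

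The cost is a few sentences, settled before unblinding. No extra data are needed and the sample size can stay as it is.

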### Randomisation and Treatment Phase

At the end of the open-label run-in phase subjects will attend for a second study visit and the following will be repeated: i) office brachial blood pressure and heart rate measurement in triplicate; ii) applanation tonometry to determine aortic pulse wave velocity; iii) applanation tonometry to derive central pressure waveforms from pulse wave analysis; iv) collection of serum and plasma for haematological and biochemical analysis; v) storage of serum and plasma at -80°C for future assay of biomarkers associated with cardiovascular function and calcification; vi) collection of a spot urine sample to determine albumin: creatinine ratio; and vii) 24-hour urine collection for determination of phosphate excretion.

Participants will then be randomised by computer assignment to continue 1600 mg (or half-dose) sevelamer with meals or receive an identical placebo for the remaining 36 weeks (Figure 1). During this blinded treatment phase subjects will undergo monitoring of renal function and serum calcium, phosphate and PTH every four weeks. Serum phosphate levels will be managed according to a pre-defined protocol during the treatment period (Table 3). All measurements performed at the initial main study visit (except for the plain lateral abdominal radiograph) will be repeated at a final visit 40 weeks after baseline studies, marking the end of subject participation in the study.

**Table 3 T3:** Management of serum phosphate levels during treatment phase

	Serum Phosphate (mmol/L)	Action
At visit	<0.8	Recheck serum phosphate within 1 week
	>0.8	Continue routine 4-weekly checks

Within 1 week of visit	<0.8	Reduce treatment/placebo dose to 800 mg tds and recheck in 2 weeks
	>0.8	Continue routine 4-weekly checks

2 weeks after visit	<0.8	Final measurements and withdraw from study
	>0.8	Continue routine 4-weekly checks

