### Subject Withdrawal

Withdrawal criteria are listed in Table 4. The average serum phosphate level of patients with stage 3 CKD enrolled in a previous study by the investigators was 1.2 ± 0.2 mmol/L [38]. It is therefore felt unlikely that significant numbers of participants will need to be withdrawn because of hypophosphataemia. The majority of patients with stage 3 CKD do not require phosphate-binding medication for overt hyperphosphataemia and the prevention of metabolic bone disease. Should any subjects in the placebo group develop serum phosphate >1.8 mmol/L, they will be withdrawn from the study and rescue therapy with appropriate phosphate binders will be administered.

**Table 4 T4:** Withdrawal criteria

Withdrawal Criteria
Pregnancy
Hypophosphataemia (serum PO_4 _<0.8 mmol/L despite dose reduction of treatment/placebo)
Hyperphosphataemia (serum PO_4 _>1.8 mmol/L in subjects receiving placebo)
Occurrence of any serious adverse event, intercurrent illness or laboratory abnormality which, in the opinion of the investigators, warrants the subject's permanent withdrawal from the study
Poor compliance with study medication
Poor attendance at study visits
Subject inability to tolerate study medication due to side effect profile
Subject decision to withdraw
Deteriorating renal function
Subject lost to follow-up (loss of contact before final study visit)

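### If repeated-measures ANOVA is applied to the four-weekly biochemistry, it drops incomplete subjects and pulls the phosphate contrast modestly toward zero; a mixed model would avoid this

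*Protocol article*

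**What the plan says.** Planned Statistical Analysis lists unpaired t-tests, χ² tests and "repeated measures analysis of variance with corrections made for multiple comparisons" for normally distributed variables. For other variables it gives log transformation or a rank test. It assigns none of these to a particular variable. It also states "Analysis will be by intention-to-treat" and gives the time points: "Comparisons will be performed between the groups at baseline and after the 36-week treatment phase".

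Under Randomisation and Treatment Phase, "subjects will undergo monitoring of renal function and serum calcium, phosphate and PTH every four weeks". Over 36 weeks that is 36/4 = 9 post-randomisation visits. Table 3 in that section ends, for phosphate that stays low after rechecks and a dose reduction, with "Final measurements and withdraw from study".

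Table 4 (Subject Withdrawal) applies the low limit to both arms, "<0.8 mmol/L despite dose reduction of treatment/placebo", but the high limit of 1.8 mmol/L only to subjects on placebo. The same section expects few withdrawals for hypophosphataemia, citing an earlier phosphate mean of 1.2 with SD 0.2 mmol/L.

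**The concern.** Classical repeated-measures ANOVA needs a value at every visit. A subject who withdraws at week 20, or misses one sample, loses the whole record, including good values already taken. That sits badly with analysing subjects as randomised.

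For phosphate the loss also depends on the outcome. A drug that lowers phosphate sends more sevelamer subjects below the low limit, and only placebo subjects can leave through the high limit. Deleting those records raises the sevelamer mean and lowers the placebo mean, so the apparent separation shrinks.

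The hypothesis is that phosphate binding changes the heart and arteries. The separation achieved is therefore needed to interpret the left ventricular mass result, whether that result is positive or null.

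**Working it through.** **The article's own figure.** Inputs from Planned Statistical Analysis: difference 8 g, SD 15 g, two-sided 5%, 80% power. n = 2 × (1.960 + 0.842)² × 15² / 8² = 55.2, so 56 per arm by formula against 55 stated. Power at 55 is 79.9% (normal) or 79.2% (noncentral t). The figure reproduces to within rounding, and nothing below changes it: with two time points, the arm-by-time test in repeated-measures ANOVA is the t-test on change.

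**Which variables are exposed.** CMR, echocardiography and DEXA are done at baseline and the final visit. The end-of-run-in visit repeats "applanation tonometry to determine aortic pulse wave velocity" and pulse wave analysis, but it precedes randomisation. Each listed endpoint thus has one scheduled post-randomisation value. Only the four-weekly biochemistry has nine.

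**Loss of subjects.** The stated 10% dropout gives 0.10 × 120 = 12 subjects lost to a complete-case analysis. If a proportion m of samples is also missed at each visit (assumed, independent of dropout), the complete share is 0.90 × (1 − m)^9. The last column is 1/√share, the standard-error ratio against 120 complete subjects. It is a ceiling on what better use of the data could recover.

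| m (assumed) | Missed samples only | With 10% dropout | SE ratio |
|---|---|---|---|
| 0 | 100% | 90% | 1.05 |
| 1% | 91% | 82% | 1.10 |
| 2% | 83% | 75% | 1.15 |
| 5% | 63% | 57% | 1.33 |

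**Direction of the bias.** With mean 1.2, SD 0.2 and normality, one placebo value is below 0.8 with probability Φ(−2) = 0.023 and above 1.8 with probability 1 − Φ(3) = 0.001. If sevelamer lowers the mean by 0.1 or 0.2 (assumed), the chance of a value below 0.8 becomes Φ(−1.5) = 0.067 or Φ(−1) = 0.159. These are single-value chances, before rechecks and dose reduction. Low-value withdrawals on placebo work the other way, but they are rarer.

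**Size of the bias.** Nine four-weekly visits were simulated with the withdrawal limits and Table 3's recheck and dose-halving steps. The table shows the contrast averaged over visits, within-subject correlation 0.6, no sporadic missing samples. The all-subject contrast falls below the assumed effect because some subjects are on the reduced dose.

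| Assumed effect (mmol/L) | All subjects | Complete cases | Shrinkage |
|---|---|---|---|
| 0.05 | 0.0499 | 0.0456 | 8.6% |
| 0.10 | 0.0984 | 0.0930 | 5.5% |
| 0.20 | 0.1909 | 0.1836 | 3.8% |
| 0.30 | 0.2735 | 0.2654 | 2.9% |

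Over correlations 0.4, 0.6 and 0.8, with 0 or 2% missed samples, shrinkage ran from 1.7% to 8.8% and was toward zero in every scenario. In absolute terms it is about 0.004-0.008 mmol/L, or 0.02-0.04 of the SD of 0.2. Simulated phosphate withdrawals were 0.6-1.6% on placebo and 0.5-5% on sevelamer.

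**Does a mixed model help?** As a stress case, the dose-reduction step was left out (correlation 0.6, 2% missed samples, effects of about 0.10, 0.20 and 0.30). Complete-case shrinkage was 13.3%, 15.1% and 17.8%. A random-intercept mixed model on all observed visits gave 0.9%, 1.2% and 1.6%. In a separate simulation with the withdrawal rules applied (correlation 0.7, 8% random dropout, 2-5% missed samples), complete cases gave 0.087-0.088 against 0.093, and 0.170-0.171 against 0.178. The mixed model gave 0.093 and 0.179.

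**The case against.** The strongest reply is that the article plans no nine-visit analysis. It compares groups at baseline and after 36 weeks, calls the four-weekly bloods monitoring, lists none of them as an endpoint, and leaves ANOVA in a generic list. That stands, and it makes the point conditional: it applies if the named method is used on those data. It is still the only repeated-data method named, and these are the only variables with repeated post-randomisation values.

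A second reply is that handling of missing data may be set out in a fuller document. That also stands, and silence on imputation is not criticised here. The point concerns the method that is named.

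Three stronger readings are tempting but unsupported:

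- A reader might infer that the primary or listed secondary analyses are compromised. They are not: repeated-measures ANOVA loses essentially the same subjects as a final-visit t-test, and there are no intermediate on-treatment values to recover. Low-phosphate withdrawals also have final measurements taken.
- A reader might infer that a quarter to two fifths of subjects will be lost. That needs 2-5% of samples missed per visit on top of 10% dropout. The article gives no missed-sample rate, and poor attendance is itself a withdrawal criterion, so the two may overlap.
- A reader might take "analysed by Mann-Whitney U or Kruskal-Wallis tests" to mean that repeated values would be ranked as if independent. Nothing in the article plans that. The half-dose option alone could give three independent groups.

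**Conclusion.** The point holds in a limited form. If repeated-measures ANOVA is used for the four-weekly phosphate, calcium, PTH or renal function, it keeps only complete subjects, which fits poorly with the intention-to-treat statement.

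For phosphate, the arm contrast is understated by about 2-9%, given assumed effects of 0.05-0.30 mmol/L, correlations of 0.4-0.8 and a working dose-reduction step. The 13-18% range is an upper case without that step. The article's expectation of few hypophosphataemia withdrawals is consistent with the lower range.

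The loss of about 12 of 120 subjects follows from the stated dropout. Any further loss depends on an unknown missed-sample rate. The change is worth making because the phosphate separation bears on how the main result is read, but no listed endpoint turns on it.

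**What to change.** In Planned Statistical Analysis, for any variable measured at more than one post-randomisation visit, replace repeated-measures ANOVA with a linear mixed model. It should use all randomised subjects and every value recorded up to withdrawal, including the recheck values that trigger withdrawal. Withdrawal then depends on data in the model, which is what makes a likelihood-based analysis suitable.

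Use fixed effects for arm, visit, arm-by-visit and baseline, and state whether baseline is the pre-run-in or the end-of-run-in value. State the covariance structure and how off-schedule rechecks enter. A random intercept admits extra records within a visit window. Analyse skewed variables such as PTH on the log scale.

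The cost is one paragraph of wording and a little programming, with no new subjects, visits or data. The small downside is having to specify a covariance structure. The model does not replace measurements after withdrawal, which would serve intention-to-treat more directly where they can be obtained.

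### A normality test on the trial data decides whether the primary analysis estimates the gram difference in left ventricular mass that the trial was sized on

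*Protocol article*

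**What the plan says.** The Endpoints section defines the primary endpoint on left ventricular mass: "The primary end-point of the study will be a reduction in left ventricular mass after 40 weeks of treatment".

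Planned Statistical Analysis then sets one decision rule for all continuous data:

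- The gate: "The normality of distribution of all continuous variables will be determined using a normality plot and the Kolmogorov-Smirnov test".
- If the variable passes: "Normally distributed variables will be analysed using unpaired t-tests", with repeated measures analysis of variance as another option.
- If it fails: "Variables not normally distributed will be log transformed prior to analysis to achieve normal distribution".
- If the transform does not work: "if this is not achieved, analysed by Mann-Whitney U or Kruskal-Wallis tests".

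The primary endpoint is not exempted, and no separate primary model is named. The next paragraph of the same section gives the sizing: "Sample size calculations were based on the primary endpoint of change in left ventricular mass after 40 weeks of treatment". The target is "detecting an 8 g difference between the change in left ventricular mass from baseline to 40 weeks", "given a standard deviation of 15 g in the change in left ventricular mass from baseline", by a two-tailed t-test at 5% with 55 per arm and at least 80% power.

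**The concern.** The sizing paragraph commits the trial to one quantity, a mean difference in grams between the arms' changes. The decision rule in the paragraph before it can move the primary analysis away from that quantity, depending on how the data look.

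Each departure changes the question. A log does not exist for a change of zero or below. A log of mass at each visit does exist, but its back-transformed contrast is a ratio of geometric means. A Mann-Whitney test compares the ordering of the two arms and gives no mean difference. A reader of the result would not know in advance whether the 8 g target was going to be estimated at all.

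**Working it through.** **Inputs.** From Planned Statistical Analysis: difference 8 g, SD of change 15 g, two-sided 5%, 80% power, 55 per arm, and a 14 g drop from baseline in the investigators' earlier spironolactone study. The article gives no expected placebo mean change, no mean left ventricular mass and no distributional shape, so anything resting on those is an assumption.

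**1. The plan's own figure.** n per arm = 2 × (1.96 + 0.8416)² × 15² / 8² = 2 × 7.849 × 225 / 64 = 55.2, so 56. The noncentral t gives 56.2, so 57. Power at 55 per arm is 79.9% (normal) or 79.2% (t). The stated 55 is reproduced within rounding, and it belongs to a gram-scale comparison of mean changes.

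**2. The log step applied to the change.** With normally distributed changes of mean m and SD 15 g, P(change ≤ 0) = Φ(-m/15):

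| Assumed mean change (g) | Zero or below | Zero or above (sign reversed) |
|---|---|---|
| 0 | Φ(0) = 50% | 50% |
| -4 | Φ(0.267) = 61% | 39% |
| -8 | Φ(0.533) = 70% | 30% |
| -14 | Φ(0.933) = 82% | 18% |

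A placebo mean of 0 and a sevelamer mean of -8 g give (50 + 70)/2 = 60% of all subjects without a defined log. Reversing the sign so that reductions count as positive does not solve the problem.

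**3. The log step applied to mass at each visit.** This can be computed, but the contrast is multiplicative. Since the article gives no mean mass, the 8 g target cannot be converted to a ratio from its figures.

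**4. The rank fallback.** In an assumed example, changes have SD 10 g around zero and 20% of treated patients fall by a further 40 g. The expected mean difference is 0.2 × 40 = 8 g. Simulation gave a mean difference of 8.1 g and a Hodges-Lehmann shift of 4.6 g. The two agree when the treatment effect is a pure shift, but not in general.

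**5. How often the gate would switch the test.** In 4,000 simulated trials per setting, with 55 per arm and the test on pooled within-arm residuals:

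| Assumed shape | Uncorrected Kolmogorov-Smirnov rejects | Lilliefors-corrected rejects |
|---|---|---|
| Normal | about 0% | 4-5% |
| t(4) | 8-10% | 49-50% |
| Gamma(2) | 40-41% | 96% |

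The article does not say which version is meant, or what happens when plot and test disagree.

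**6. Error rate and power of the two-stage rule.** These runs omit the log step: t-test if the gate is passed, Mann-Whitney if not. With the corrected test and 55 per arm, type I error was 4.7% to 5.4%. Two further sets with the uncorrected test and 54 per arm gave 4.1% to 5.5% and 4.6% to 5.8%. The 5.8% came from t(3) data in 3,000 runs, with a Monte Carlo error of about 0.4 points. Power for an 8 g shift with the corrected test was 78.7% on normal data (plain t-test 78.7%), 88% on t(4) data (80%) and 91% on gamma(2) data (79%).

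**The case against.** The defence has real substance.

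- **The log branch is not a dead end.** A reader might infer that part of the plan cannot be carried out. The article never says that the change score is what gets logged. It also compares groups at each time point and lists repeated measures analysis of variance, both of which can use mass at each visit. That log exists, and the rank tests catch whatever remains. What stands is that neither route yields the gram difference.
- **The error rate is not shown to suffer.** A reader might infer inflated false positives from testing in two stages. The simulations show none of material size, and no loss of power. Under a pure shift with non-normal data, the rank route gains power.
- **The timing and target of the check are not stated.** A reader might infer that the test is chosen after unblinding, or that normality is checked on the pooled raw variable. The text supports neither: it does not say when the check is made, or whether it is pooled, by arm or on residuals.
- **Lack of baseline adjustment is not specific to Mann-Whitney.** The planned unpaired t-test does not adjust either.
- **A full analysis plan may exist.** Details such as the version of the test can properly sit there. But the article does not leave the choice of analysis open. It states a rule for all continuous variables, and that rule does not fit its own sizing. If an unseen plan already names a single primary analysis, only the article's wording needs to be brought into line.

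**Conclusion.** The point holds in a limited form. The stated rule lets the observed data decide whether the primary analysis estimates the mean gram difference behind the 55 per arm, a ratio, or a rank-based contrast. The harm is an unfixed primary test and estimand, not an inflated error rate or lost power.

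That a signed change cannot be logged is certain. The 50% to 70% share depends on the assumed mean changes of 0 to -8 g and on normality with the protocol's SD. The switching frequencies and the 8.1 g against 4.6 g contrast depend on assumed shapes that the article does not give. If the changes are close to normal, the gate will usually leave the t-test in place (rejection in about 0% to 5% of trials) and the practical effect will be small.

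**What to change.** For left ventricular mass, and for the other endpoints defined as a change, remove the normality gate and fix one analysis in advance whatever the distribution: the mean difference between arms at 40 weeks on the original scale, adjusted for the baseline value (ANCOVA, with robust standard errors if wished), with a 95% confidence interval. List rank-based, permutation or log-scale analyses as sensitivity analyses only.

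The cost is wording. Baseline mass is already measured in every subject, and the sample size stays as planned. Adjustment uses one degree of freedom. With equal variances at the two visits and baseline-to-follow-up correlation ρ, the variance relative to an unadjusted comparison of changes is 2σ²(1 - ρ) reduced to σ²(1 - ρ²), a factor of (1 + ρ)/2, which cannot exceed 1. Precision can improve and is not materially put at risk. What is given up is the extra power that a rank test would have as the primary test under a pure shift with markedly non-normal data. The sensitivity analysis would still show that result.

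### The multivariable models for left ventricular mass and stiffness are to be built by stepwise selection, which exaggerates weak predictors at about 110 subjects; fixed models should replace it (minor, does not touch the primary t-test)

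*Protocol article*

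**What the plan says.** The Planned Statistical Analysis section of the protocol article contains two separate strands.

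- **Between-group comparison.** "Normally distributed variables will be analysed using unpaired t-tests", with chi-square, repeated measures analysis of variance and rank tests as the other options. The sample size rests on this strand: "55 subjects in each arm will provide at least 80% power of detecting an 8 g difference", "using a two-tailed t-test at the 5% significance level", "given a standard deviation of 15 g in the change in left ventricular mass from baseline". The section adds "Analysis will be by intention-to-treat".
- **Regression.** "Multiple linear regression models will be derived for left ventricular mass and measures of vascular and cardiac stiffness using stepwise regression analysis". The article does not list the candidate variables, give the entry and removal rule, or say whether the models are exploratory.

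One threshold serves both strands: "A p-value of <0.05 will be considered statistically significant". The remark about correcting for multiple comparisons belongs to the sentence on t-tests and analysis of variance, not to the regression sentence.

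Left ventricular mass is the primary endpoint variable in the Endpoints section. Arterial stiffness and ventricular elastance are among the secondary endpoints.

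**The concern.** The article chooses stepwise selection outright, so this is a stated method and not a detail left for an analysis plan. A later plan could add a candidate list and entry limits, but ordinary p-values and intervals taken from the selected model would still ignore the selection.

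Two consequences follow. A variable enters only when its estimate in this sample is large enough, so the coefficients that survive are too large on average. The printed confidence intervals treat the selected model as if it had been chosen in advance, so for weak predictors they can miss the true value more often than 5% of the time. With the 5% rule applied without qualification, readers would take the retained variables as independent determinants of left ventricular mass or stiffness, of about the size shown.

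**Working it through.** **1. The sample size, to fix n.** Inputs from the article: difference 8 g, SD 15 g, two-sided 5%, 80% power. The normal approximation gives n = 2 × (1.96 + 0.84)² × 15² / 8², which rounds up to 56 per arm, against 55 stated. Power at 55 per arm is 79.9% (normal) or 79.2% (exact t). The stated figure is reproduced within rounding. Evaluable n is 2 × 55 = 110. Taking 10% off 60 per arm gives 54 per arm, or 108. The results below were obtained at 108 or 110, and the difference is immaterial.

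**2. Assumptions that the article does not supply.** Ten independent, normally distributed candidates; entry at p<0.05; where removal was simulated, removal at p>0.10. One candidate has a true standardised slope and the other nine have none.

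**3. Simulated stepwise results (800 runs per slope, N = 110).**

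| True slope | Retained in | Mean when retained | Ratio | 95% CI coverage when retained | Fixed 10-covariate model, mean |
|---|---|---|---|---|---|
| 0.1 | 19% | 0.24 | 2.4 | 83% | 0.101 |
| 0.2 | 51% | 0.27 | 1.4 | 94% | 0.198 |
| 0.3 | 85% | 0.33 | 1.09 | 97% | 0.300 |

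A separate run at n = 108 gave 0.24 with 81% coverage for the slope of 0.1, where the fixed full model gave 0.10 with 94%. The 81% and 83% do not differ beyond simulation error: about 0.189 × 800 = 151 retained runs gives a standard error of √(0.83 × 0.17 / 151) = 3 percentage points.

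**4. Check by formula.** Take SE = 1/√110 = 0.0953, critical value c = 1.98 and m = slope/SE. The mean of an estimate kept only when |estimate/SE| > c is

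slope + SE × [φ(c − m) − φ(c + m)] / P(retained).

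- Slope 0.1: m = 1.049, P = 0.177, so 0.1 + 0.0953 × (0.2586 − 0.0041)/0.1771 = 0.237.
- Slope 0.2: m = 2.098, P = 0.547, so 0.2 + 0.0953 × 0.396/0.547 = 0.269.
- Slope 0.3: m = 3.146, P = 0.878, so 0.3 + 0.0953 × 0.202/0.878 = 0.322.

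These agree with the simulated means.

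**5. In grams, as an illustration.** If the outcome were change in left ventricular mass with the article's SD of 15 g, a slope of 0.1 is 0.1 × 15 = 1.5 g per SD of the predictor. When retained it would be reported on average as 0.24 × 15 = 3.6 g.

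**6. What a fixed model gives.** With treatment and three prespecified covariates at N = 110 (4,000 runs), the simulated type I error for treatment is 0.050.

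**The case against.** The strongest objection is that nothing of consequence rests on these models. That largely stands, and it limits the point in four ways.

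- **The treatment comparison is elsewhere.** A reader might infer that the primary test is compromised because the treatment term could be dropped or kept only when large. The article does not support this. The groups are compared by t-test or its alternatives, the trial is powered on the t-test, and the regression sentence never mentions the randomised arm.
- **The chance of a false predictor is not specific to stepwise selection.** A reader might point to simulated rates of 30%, 49% and 65% for at least one false predictor among 8, 12 and 20 null candidates. Ordinary multiplicity explains them: 1 − 0.95^k gives 34%, 46% and 64%, and a fixed model holding the same covariates gives 34%, 43% and 60%. Shortening the list lowers these rates; fixing the model alone hardly does.
- **An inflated treatment effect is not specific to it either.** A true 8 g effect averages about 9.1 g among significant results of a plain t-test with 54 per arm. With arm as one of 10 stepwise candidates it is kept in 78% of runs and averages 8.9 g. That is the effect of any significance filter.
- **The role of the models is not stated.** A reader might infer that they carry the trial's explanatory claim about phosphate. The Summary ties its conclusion to a positive effect of the intervention and does not mention regression.

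It is also fair to say that a model with arm and baseline value answers a different question from a model of determinants, so the fix must leave room for the latter. What survives the objection is the bias of retained coefficients and the under-coverage for weak ones. Both are specific to reporting a selected model, and a fixed model avoids both.

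**Conclusion.** The point holds as a minor one about supporting analyses. Stepwise selection is the stated method, and at about 110 subjects it exaggerates weak predictors substantially: about 2.4-fold at a standardised slope of 0.1 and about 1.4-fold at 0.2. For a strong predictor the harm is small, about 9% at 0.3. Under-coverage of the intervals appears at the weak end only (81 to 83% at a slope of 0.1) and not at 0.2 or 0.3. The primary between-group test and the sample size are not affected.

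The sizes rest on 10 independent candidates and entry at p<0.05, both assumed. A different list, correlated candidates or another entry rule would change the figures. As long as entry depends on the observed estimate, the direction of the bias for weak predictors would be expected to remain.

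**What to change.** Replace stepwise selection with one fixed model per outcome: the week-40 value regressed on randomised arm and baseline value, both always included, plus a short list of covariates named before unblinding. All can come from data already collected, for example age, baseline estimated GFR, baseline ambulatory systolic pressure and baseline serum phosphate. Report every coefficient with its 95% confidence interval, whether or not it reaches 5%. If a data-driven model of determinants is still wanted, keep it separate, label it exploratory and exempt it from the 5% significance rule.

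The change needs no extra subjects, visits or measurements and leaves the planned t-test as it is. The cost is agreeing the covariate list in advance, and fewer variables can be screened.
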